##### Power calculation for serious cardiovascular adverse events

In order to test the hypothesis for serious cardiovascular adverse events as for the primary endpoint at a one-sided alpha = .05 when the non-inferiority margin is 1.5, the final sample size of 3000 to 3300 subjects will provide at least 62% power, assuming a hypothetical rate of events of 3.43%, or 103 to 113 cardiovascular serious adverse events.

##### Power calculation for efficacy analysis

With an expected 0.5% difference in mean change in HbA1c levels between the two treatment groups and a standard deviation of HbA1c level of 1.0% and the baseline and 24 week scores have a correlation of 0.50 then the effect size is 0.5%/1.0% = 0.50. For the metformin/sulphonylurea analysis, 160 subjects assuming a standard deviation of 1.0% will provide a power of 90% power to detect differences in mean changes of 0.5% or larger.

### Endpoints

#### Safety

• The primary safety endpoint is the rate of time to first treatment emergent all-cause serious adverse events.

• Secondary safety endpoints include disease-specific rate of time to first treatment emergent serious cardiovascular adverse events (myocardial infarction, stroke, inpatient hospitalization for heart failure or angina, and revascularization surgery) and the individual specific rates.

#### Efficacy

Other clinical measures include the impact (either positive or negative) of Cycloset™ on HbA1c, fasting plasma glucose, weight, triglycerides lipids, blood pressure and patient tolerability after six months of therapy. Inasmuch as concurrent diabetes medications may change over the 52 week period with greater probability than at 24 weeks, the primary efficacy analyses will be based on changes from baseline to 24 weeks of treatment.

### Statistical analysis – safety and other clinical measures

#### Safety

The Intention-To-Treat (ITT) analysis set will include all subjects who were randomized to the study and received at least one dose of study treatment (either Cycloset™ or placebo) and will be used for evaluating all safety endpoints. The Evaluable Per-Protocol (EPP) analysis set will consist of those ITT subjects with no major protocol violations and with at least one post-randomization measurement of HbA1c, fasting plasma glucose, lipids, weight, waist circumference or blood pressure. The primary analysis tested the hypothesis that the occurrence of all-cause serious adverse events for Usual Diabetes Therapy (UDT) plus Cycloset™ is not inferior to that for UDT plus placebo by a predefined margin. For this study, the predefined margin of non inferiority was defined as a hazard ratio (UDT plus Cycloset^® ^versus UDT plus placebo) of 1.5. The hazard ratio and one-sided 96% confidence interval will be obtained from the Cox regression model with treatment and center effects. The non-inferiority will be supported by the result that the upper bound of the confidence interval is below 1.5. The proportional hazards assumption underlying the Cox model will be examined with appropriate alternative statistical models applied. Results based on the ITT analysis set will be considered primary and those based on EPP analysis supportive. The secondary safety endpoint is the time to the occurrence of first cardiovascular SAEs (myocardial infarction, stroke, in-patient hospitalization for heart failure, angina or revascularization surgery). These endpoints will be analyzed in the same manner as described above for the primary endpoint

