#### Patient follow-up procedures

After screening, patients were randomized and titrated to the maximum tolerated dose of the study drug over a six week period. After titration, subjects were seen every 3 months until study end (week 52) or early termination. Subjects were contacted 30 days after completion of study drug to record any adverse events occurring after treatment completion. See table 2 for visit schedule and assessments.

**Table 2 T2:** Study Flow Sheet

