			**STUDY WEEK**												
		-2	-1	0	1	2	3	4	5	6	12	24	36	52	Termination^3^

Assessment and Measurement	Pre-Screen	Screen	♠												

HbA1c: Local lab < 10	♣	♣													
Clinic Visit		X		X			X			X	X	X	X	X	X
Medical History		X													
Concomitant Meds and Illnesses		X					X			X	X	X	X	X	X
Pregnancy test*		X													
Full Physical Exam, *(Weight & Waist Circumference)*^1^		X										X		X	X
Blood pressure		XX		X			X			X	X	XX	X	X	X
Record Adverse events (AE)				X			X			X	X	X	X	X	X
ECG		X										X		X	X
Telephone Call to Subject for AE's Reports					X	X		X	X						
CBC & Plasma Sample		X										X		X	X
Chemistry, LAE♥		X^⊕^								X		X		X	X
HbA1c		X									X	X	X	X	X
Fasting Plasma Glucose^2^		X		X			X			X	X	X	X	X	X
Fasting Lipid Profile^♦2^		X										X		X	X

Notes on measures

♣ Local lab documentation of HbA1c ≤ 10 must be confirmed within 12 wks prior to conducting the Week-2 screening visit tests

♠ During Week-1 any labs or tests unable to be performed at screening should be completed

* To include pregnancy test (beta-HCG) in women of childbearing potential.

♥ CBC with differential and platelets, urinalysis, liver function (ALT, AST, alkaline phosphatase and total bilirubin), BUN, creatinine, Na, K, Cl, bicarbonate, calcium, phosphorus, and albumin.

♦ Total cholesterol, triglycerides, HDL-cholesterol, and LDL-cholesterol.

1. for body mass index and waist circumference to be measured on subject in the supine position at the level of the umbilicus

2. for BMI Obtained in the morning after a minimum 8 h overnight fast

3. A full 52-week assessment must be performed whenever a subject *terminates *the study early.

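### The supportive per-protocol analysis of serious adverse events (SAEs) requires an efficacy or vital-sign measurement that the endpoint does not need, and it cannot test whether uncounted SAEs after early leaving matter

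*Protocol article*

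**What the plan says.** All references are to the Protocol article.

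- **Statistical analysis, Safety.** The ITT set is "all subjects who were randomized to the study and received at least one dose of study treatment" and serves all safety endpoints. The EPP set is the part of ITT with "no major protocol violations and with at least one post-randomization measurement of HbA1c, fasting plasma glucose, lipids, weight, waist circumference or blood pressure". On rank: "Results based on the ITT analysis set will be considered primary and those based on EPP analysis supportive".
- **Endpoints, Safety.** "The primary safety endpoint is the rate of time to first treatment emergent all-cause serious adverse events".
- **Patient follow-up procedures.** "After titration, subjects were seen every 3 months until study end (week 52) or early termination". Also: "Subjects were contacted 30 days after completion of study drug to record any adverse events occurring after treatment completion".
- **Table 2, note 3.** "A full 52-week assessment must be performed whenever a subject" leaves the study early. The Termination column includes adverse events, blood pressure, weight and waist, HbA1c, fasting glucose and lipids.
- **Table 2, schedule.** After week 0, the first scheduled visit with any of the measurements named for EPP is week 3 (blood pressure and fasting glucose).

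The article describes no follow-up of early leavers to week 52 beyond these provisions.

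**The concern.** Two separate mechanisms are involved, and they affect different people.

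**Membership of EPP.** The measurement condition suits an efficacy analysis. The metformin/sulfonylurea sub-study has a similar one, a week-24 HbA1c, for its own per-protocol set. For time to first SAE it serves no purpose, and it makes membership depend partly on the outcome: a fatal or disabling early SAE can be the reason why no measurement exists.

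**Events after leaving.** The primary analysis is called ITT, but a treatment-emergent endpoint with visits ending at early termination makes it close to an on-treatment count. Study drug is titrated to the maximum tolerated dose over six weeks, so leaving for poor tolerability could differ by arm. If those who leave are also at higher SAE risk, censoring them lowers the observed hazard ratio and makes the 1.5 margin easier to meet.

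The supportive analysis ought to show whether the primary result is robust. On the second mechanism it cannot, because it applies the same endpoint and censoring to a subset of the same subjects.

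**Working it through.** **1. The plan's own figure.** Inputs from the sample size section and the study design: one-sided alpha 0.05, power 0.90, margin 1.5, allocation 2:1. The number of events is (z0.95 + z0.90)² / [(ln 1.5)² × (2/3)(1/3)] = (1.645 + 1.282)² / (0.4055² × 0.2222) = 234.4, so 235. This matches the plan. Dividing by the 0.08 rate gives 235/0.08 = 2,938 subjects, within 2% of the stated 2,991. The sample size is not at issue here.

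**2. Ceiling on events that EPP can lose.** Inputs: 3,095 randomised; 8% at one year, applied to both arms; constant hazard (assumption); first scheduled measurement at week 3.

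- Expected events: 3,095 × 0.08 = 247.6, about 248.
- Events in weeks 0 to 3: 247.6 × 3/52 = 14.3, about 14 (5.8%).

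This is a ceiling. A subject with an SAE in week 2 who attends week 3, or has a termination assessment, stays in EPP with the event unless there is a major violation. Only those with no post-randomisation measurement at all are lost.

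Loss in the same proportion in both arms leaves the ratio unchanged. In the most extreme case, where every week 0–3 event on drug is lost and none on placebo, the EPP ratio is multiplied by 1 − 3/52 = 0.942, so 1.50 would appear as about 1.41. Nothing in the document suggests that this would happen.

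**3. What uncounted later events could do to the primary analysis.** The document gives no dropout rate, so every input here is an assumption. A fraction d leaves and is unobserved for half a year on average; the hazard after leaving is r times that before, in both arms. Relative events per subject over the full year are F = (1 − d/2) + r·d/2. If the full-year ratio is 1.5, the observed on-treatment ratio is 1.5 × F(placebo)/F(drug).

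| Leave, drug / placebo | r | F placebo | F drug | Observed ratio |
|---|---|---|---|---|
| 30% / 30% | 2 | 1.15 | 1.15 | 1.50 |
| 30% / 20% | 1 | 1.00 | 1.00 | 1.50 |
| 30% / 20% | 2 | 1.10 | 1.15 | 1.43 |
| 40% / 25% | 2 | 1.125 | 1.20 | 1.41 |
| 30% / 20% | 3 | 1.20 | 1.30 | 1.38 |

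The chance of wrongly declaring non-inferiority is Φ[ln(1.5/observed) × √(D × 2/9) − z]. With D = 235, √(235 × 2/9) = 7.23. For 1.43 (1.4348 unrounded): 0.0445 × 7.23 − 1.645 = −1.32, or 9%. For 1.38 (1.3846 unrounded): 0.0800 × 7.23 − 1.645 = −1.07, or 14%. Both compare with a nominal 5%. With the one-sided 96% interval named in the analysis section (z = 1.751) they are 8% and 12% against 4%. The bias is zero unless leaving differs by arm and the risk after leaving is raised.

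**4. Would counting everything to week 52 remove the problem?** Not by itself. Suppose the on-drug ratio is 1.5, the excess ends on stopping, risk is not otherwise raised (r = 1), and 30% leave the drug arm for half a year on average. The full-year ratio is 1.5 × 0.85 + 1 × 0.15 = 1.425. Time off drug also pulls towards non-inferiority, by a similar amount.

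**5. Are these the same people?** No. Anyone who leaves after the week-3 visit already has a blood pressure or glucose value and meets the EPP measurement condition. Leaving around the end of titration therefore concerns the second mechanism only.

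**The case against.** - **ITT is primary and complete.** It holds every dosed subject and counts SAEs up to leaving, including one that causes withdrawal. A reader might infer that the SAEs of early leavers drop out of both safety analyses. The document does not support that; only events after leaving, beyond any 30-day contact, are at issue. This objection stands.
- **The termination assessment supplies the measurement that EPP needs.** This also stands, and it reduces the EPP problem to deaths and non-returners before week 3. It does not remove it.
- **EPP is only supportive.** True, and it limits the consequence. It does not justify a condition that the endpoint does not need.
- **A treatment-emergent endpoint is a legitimate choice for drug safety.** It is. Step 4 shows that a week-52 count regardless of treatment has its own lean, so replacing the primary endpoint would be a trade-off and not a correction.
- **A condensed article may leave the event window, censoring rules and follow-up of leavers to the full protocol or analysis plan.** This is fair, and their absence is not counted as a fault here. The text also speaks of terminating the study, which is not the same as stopping drug, and it is unclear whether the 30-day contact covers those who stop early. What the article does fix is the EPP definition, the treatment-emergent endpoint and the end of visits at early termination.

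**Conclusion.** The point holds in a limited form. The EPP set for SAEs carries a measurement condition that can remove a subject together with the event. The size is at most about 14 of about 248 expected events, assuming a constant hazard and 8% in both arms, and probably far fewer because most leavers will have a termination assessment.

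The primary analysis does not count SAEs well after early leaving. It would be tempting to conclude that the primary result is biased towards non-inferiority. The document gives no dropout rate, no difference between arms and no link between leaving and SAE risk, so the observed ratios of 1.38 to 1.43 for a true 1.5 are illustrations under assumed inputs. With equal leaving, or no raised risk after leaving, there is no bias. What can be said is that the possibility exists and that the EPP analysis, sharing the endpoint and censoring, does not test it.

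**What to change.** 1. **Statistical analysis, Safety.** For safety endpoints, define EPP as all dosed subjects without major protocol violations, with no measurement condition. Keep that condition for efficacy analyses if wanted. This costs wording only.
2. **Endpoints, Safety, and Statistical analysis, Safety.** Keep the treatment-emergent primary analysis. Beside it, add a sensitivity analysis of time to first SAE from randomisation to week 52 that counts every SAE on record whatever the treatment status, using the same Cox model and margin. Obtain the SAE status of early leavers where that is still possible. The article describes visits in the past tense, so this may be limited to events already recorded.

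The cost is a little more analysis work and perhaps some contacts with early leavers. The added analysis is diluted by time off drug, which is why it should stand beside the primary and not replace it. Agreement between the two would be reassuring; a clear difference would show that handling of early leavers matters to the conclusion. Both changes should be fixed before unblinding.

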#### Other clinical measures

Clinical efficacy analyses will also be conducted for subjects taking any oral hypoglycemic agent (OHA) or injectable insulin secretagogue with a baseline HbA1c of ≥ 7.5%. Additional subsets of this population include those receiving a) metformin with or without any OHA or injectable insulin secretagogue and b) sulphonylurea with or without any OHA or injectable insulin secretagogue. The difference in the change in the HbA1c from baseline to 24 weeks between Cycloset™ and placebo will be the primary efficacy measure. The analyses will be based on both a) ITT – last observation carry forward method and b) subjects with an HbA1c measurement at week 24 (completers). An analysis of covariance (ANCOVA) model will be used to test for a treatment difference while adjusting for the baseline hemoglobin A_1c _value and center effect. Additional analyses will be used to assess the impacts from additional risk factors by including additional terms such as age, gender, body mass index at baseline, duration of disease history, and concomitant medications. Any significant effects from these potential risk factors will be further investigated. Analyses of treatment group differences in change from baseline in fasting plasma glucose, weight, waist circumference, triglycerides, lipid profile, and blood pressure will be explored within these defined groups.

We will also provide descriptive statistics on the changes in concomitant diabetes medications during the observational period (proportion of subjects adding therapy or increasing dose of preexisting therapy; proportion stopping therapy or decreasing dose; proportion not changing therapy). If warranted, additional analyses will assess the impact of such changes in concomitant diabetes medications during the observation period on difference between Cycloset™ and placebo in change from baseline in HbA1c.

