**Methods/Design:**

3,095 individuals were randomized in a 2:1 ratio into a one year trial aimed to assess the safety and efficacy of Cycloset™ compared to placebo among individuals receiving a variety of treatments for type 2 diabetes. Eligibility criteria for this randomized placebo controlled trial included: age 30–80, HbA1c ≤ 10%, diabetes therapeutic regimen consisting of diet or no more than two hypoglycemic agents or insulin with or without one additional oral agent (usual diabetes therapy; UDT). The primary safety endpoint will test the hypothesis that the rate of all-cause serious adverse events after one year of usual diabetes therapy (UDT) plus Cycloset™ is not greater than that for UDT plus placebo by more than an acceptable margin defined as a hazard ratio of 1.5 with a secondary endpoint analysis of the difference in the rate of serious cardiovascular events, (myocardial infarction, stroke, coronary revascularization or hospitalization for or angina or congestive heart failure). Efficacy analyses will evaluate effects of Cycloset™ versus placebo on change from baseline in HbA1c, fasting glucose, body weight, waist circumference, blood pressure and plasma lipids.

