**Discussion:**

This study will extend the current data on Cycloset™ safety, tolerability and efficacy in individuals with type 2 diabetes to include its effects in combination with thiazolodinediones, insulin secretagogues, metformin, alpha-glucosidase inhibitors and exogenous insulin regimens.

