### Study design and setting

This is a double blind, multi-center, placebo-controlled, parallel group, non-inferiority study in subjects with type 2 diabetes, comparing usual diabetes therapy (UDT) plus Cycloset™ to UDT plus placebo. Following a two-week lead-in period, 3,095 subjects were randomized in a 2:1 ratio to UDT plus Cycloset™ or UDT plus placebo across 73 clinical centers in the United States and Puerto Rico. Subjects were expected to remain on study treatment for 12 months, the first six weeks of which constitute a dose titration period.

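### The only specified between-arm comparisons of glucose, weight, waist, lipids and blood pressure are exploratory ones in oral-agent or secretagogue subgroups with HbA1c of at least 7.5%, although the aim is stated without that limit

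*Protocol article*

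**What the plan says.** **The rule.** Under Statistical analysis, Other clinical measures, the article defines a population of subjects on any oral hypoglycaemic agent or injectable insulin secretagogue with baseline HbA1c of 7.5% or more, with a metformin and a sulphonylurea subset. It then says that treatment differences in "change from baseline in fasting plasma glucose, weight, waist circumference, triglycerides, lipid profile, and blood pressure will be explored within these defined groups". The Metformin/sulfonylurea efficacy analysis section repeats the exploration of these measures in its own set, which has the same HbA1c threshold.

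**The aim.** The Abstract (Methods/Design), after describing the randomised trial, says that the work on efficacy is meant to assess "effects of Cycloset™ versus placebo on change from baseline in HbA1c, fasting glucose, body weight, waist circumference, blood pressure and plasma lipids". The Efficacy paragraph under Endpoints says "Other clinical measures include the impact (either positive or negative) of Cycloset™ on HbA1c, fasting plasma glucose, weight", and goes on to lipids, blood pressure and tolerability at six months. Waist is not in that second list. Neither statement names a subgroup. The Abstract's Discussion says that the study will widen what is known about safety, tolerability and efficacy "to include its effects in combination with thiazolodinediones, insulin secretagogues, metformin, alpha-glucosidase inhibitors and exogenous insulin regimens".

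**Who is in the trial.** Study design and setting reports that "3,095 subjects were randomized in a 2:1 ratio to UDT plus Cycloset™ or UDT plus placebo". Study interventions admits diet alone, up to two oral agents, or insulin with or without one oral agent. Table 1 sets an upper HbA1c limit of 10 and no lower limit. Table 2 schedules weight, waist, blood pressure, fasting glucose and lipids at screening and week 24 for subjects generally.

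**The concern.** The stated aim and the specified analysis do not cover the same people. A threshold of 7.5% has an evident purpose for HbA1c, because it leaves room for a fall. The article gives no reason to apply it to blood pressure, weight, waist or lipids, and the Analysis of efficacy objective attaches it to HbA1c alone.

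Two things are at stake, both in exploratory results. One is coverage: some regimens and the whole lower HbA1c range contribute nothing to any specified estimate of these effects, whether favourable or unfavourable. The other is precision, since data already collected on the remaining subjects are not used in a specified comparison.

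**Working it through.** **1. Who has a specified comparison of these measures**

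| Baseline group | HbA1c ≥ 7.5% | HbA1c < 7.5% |
|---|---|---|
| Diet only | none | none |
| Oral agent(s) or injectable secretagogue, no insulin | yes | none |
| Insulin plus one oral agent | yes, on the wording (any oral agent) | none |
| Insulin only | none | none |

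The metformin/sulfonylurea set lies within the second row. This loss of coverage does not depend on how large the groups are.

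**2. The article's one efficacy size figure**

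Power calculation for efficacy analysis gives 160 subjects, a difference of 0.5, an SD of 1.0 and 90% power, for HbA1c in the metformin/sulphonylurea analysis. Alpha and sidedness are not stated there. With 2:1 allocation, SE = SD × sqrt(3/n + 1.5/n) = SD × sqrt(4.5/n).

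- For n = 160, SE = sqrt(4.5/160) = 0.1677.
- Assuming one-sided alpha of 0.05, power = Φ(0.5/0.1677 − 1.645) = Φ(1.337) = 0.909.

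The stated 90% is therefore reproduced under that assumption. The figure says nothing about the size of the wider oral-agent group, which the article does not give.

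**3. Loss of precision relative to all subjects**

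Inputs: N = 3,095 and 2:1 allocation (Study design and setting). The share f is an assumption. With n = f × N, the SE ratio is sqrt(N/n) = 1/sqrt(f). The standardised difference detectable with 90% power at two-sided 0.05 is (1.960 + 1.282) × sqrt(4.5/n).

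| Assumed f | n | SE in SD units | SE ratio | Detectable difference (SD) |
|---|---|---|---|---|
| 100% | 3,095 | 0.0381 | 1.00 | 0.124 |
| 75% | 2,321 | 0.0440 | 1.15 | 0.143 |
| 50% | 1,548 | 0.0539 | 1.41 | 0.175 |
| 25% | 774 | 0.0763 | 2.00 | 0.247 |
| 10% | 310 | 0.1206 | 3.16 | 0.391 |

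For the metformin/sulfonylurea set at its planned 160, the ratio is sqrt(3,095/160) = 4.40. That factor belongs to the sub-study alone.

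**The case against.** The strongest reply is that the article never says these measures are compared only in the subgroups. The subgroup paragraph is introduced with the word *also*. The per-protocol set is drawn from the whole ITT set and requires a post-randomisation value of one of these same measures. The closing paragraph promises further analysis of the large study. The article is a condensed account, and its full protocol and analysis plan are not at hand. A reader might infer that a full-set analysis is ruled out. The documents do not support that, and the point here is limited to what is specified. Still, the text before *also* describes safety analyses only, so the word most naturally adds efficacy to safety. The per-protocol requirement is a condition for membership of a set and not a comparison. The closing promise fixes nothing.

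Second, subgroup efficacy is openly declared in the Background and in Analysis of efficacy, so a plain contradiction with the Abstract would be too strong a claim. This stands. What remains is that the Abstract and the Efficacy paragraph carry no such limit for these measures.

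Third, laboratory values and vital signs are additional safety parameters, and the full ITT set serves all safety endpoints. Lipid and blood pressure data may therefore be reported for everyone as safety data. This answers part of the worry about missing harm. However, the article describes no between-arm comparison of change there, and that list does not name weight or waist.

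Fourth, a reader might take the Abstract's Discussion to promise estimates for each drug class, or conclude that thiazolidinedione and alpha-glucosidase inhibitor users are left out. Neither follows. Users of those oral agents with HbA1c of at least 7.5% are inside the any-oral-agent group, and the sentence also covers safety, which is assessed across all regimens. Of the regimens it names, insulin without an oral agent is the one with no specified comparison of these measures.

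**Conclusion.** The point holds as a mismatch between the stated aim and the specified analysis population. Diet-only subjects, insulin-only subjects and all subjects below 7.5% have no specified comparison of these measures, whatever the group sizes.

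The loss of precision is 1/sqrt(f), from 1.15 to 3.16 over an assumed share of 75% down to 10%. A reader might go further and say that most of the trial's information is discarded. That needs f below 50%, which the article does not establish, and the 4.40 factor cannot stand in for the wider oral-agent group.

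The measures are labelled exploratory. The primary serious-adverse-event test, the cardiovascular endpoint and the HbA1c efficacy analysis are unaffected. This is an inexpensive improvement to secondary information and no threat to the trial's main conclusion.

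**What to change.** In Other clinical measures, replace the last four words of the sentence quoted at the start with: *in the full ITT set and, in addition, within the groups defined above*. Specify a week-24 ANCOVA for each measure, adjusted for that measure's own baseline value and for centre as in the HbA1c model, and label the results exploratory.

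If a full-set comparison is not wanted, limit the statements in the Abstract (Methods/Design and Discussion) and in the Efficacy paragraph under Endpoints to the populations that will be analysed.

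The cost is a change of wording and a few more exploratory tables, with correspondingly more unadjusted comparisons to read with caution. The data are already scheduled, so no extra subjects or visits are needed.
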